#### Diet and Behavior Scale

A 29-item questionnaire called the Diet and Behavior Scale is used to gauge people’s intake of typical dietary components. The Diet and Behavior Scale’s first component focuses on the respondent’s typical frequency of consumption of common foods and beverages. The answers to the questions are given on a scale of 1 to 5, with 1 being “never,” 2 “once a month,” 3 “once or twice a week,” 4 “most days,” and 5 “every day.” The second segment is open ended and looks into the normal serving sizes for 11 popular foods and beverages [51].

#### Other Tools, Follow-Up, and Engagement

Tools other than the Perceived Ease of Use questionnaire and Client Satisfaction Questionnaire–8 will be used before and after the digital health intervention to assess its usefulness. Individuals will be followed up for a period of 3 months at regular intervals to assess adherence to the well-being modules provided in the digital health intervention. Engagement with the digital health intervention will be assessed by monitoring the number of weekly logins, completion of tasks in a timely manner, and submission of regular data.

### Data Analysis

The baseline data for generating the well-being profile include sociodemographic profile, college profile, health status profile, familiarity with technology, and health behavior. Outcome variables will be assessed using the General Well-Being Schedule, Multidimensional Scale of Perceived Social Support, Personal Health Questionnaire Depression Scale, Perceived Stress Scale, Work-Family Conflict Scale, Client Satisfaction Questionnaire–8, Perceived Ease of Use questionnaire, General Self-Efficacy Scale, Nutrition Behavior Scale, and Stigma Scale. A descriptive analysis will be carried out using the baseline data; also, cross tabulation of sociodemographic factors with variables gathered from the instruments will be done. Two FGDs will be conducted per site to assess the perception of students on how their well-being can be addressed. Thematic analysis will be done in accordance with AMEE Guide No. 131 for qualitative data collected through FGDs [52]. For continuous variables, means and SDs will be reported, and for categorical variables, frequencies will be calculated. All statistical analysis will be performed using SAS (version 9.3; SAS Institute), and results will be reported as *P* values and 95% CIs.

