### Study Objective

The objective of the study is to design, develop and pilot-test a digital health platform to enhance student well-being. The study aims are (1) to identify multiple determinants and factors impacting well-being among undergraduate and graduate students; (2) to design and develop a digital health intervention based on the HBM, incorporating the findings of aim 1 to address the well-being issues among undergraduate and graduate students; (3) to evaluate the feasibility and acceptance of the proposed digital health intervention; and (4) to evaluate the role of the digital health intervention, as well as the roles of adherence to and engagement with it, in enhancing the well-being of undergraduate and graduate students.

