## Methods

### Study Design and Population

For aim 1, a cross-sectional study will be conducted to identify multiple determinants affecting the well-being of the students. Five thousand participants will be recruited across Gujarat and Tamil Nadu, India. Current undergraduates and graduates will be recruited from Parul University in Vadodara, Gujarat, as well as Panimalar Medical College Hospital and Research Institute, Panimalar Engineering College, Panimalar Institute of Technology, and Panimalar College of Nursing in Chennai, Tamil Nadu, using a convenience sampling approach. The participants will be recruited from their respective institutes with prior permission from their departments. The survey will be filled out by the students using their mobile devices or from the computer labs of the institutes. The survey will consist of validated tools, which are described in Multimedia Appendix 1 [35-37].

For aim 2, we will use a mixed methods approach and a quasi-experimental research design to gather data. Baseline data will be collected from aim 1 using predefined questionnaires and validated tools. Additionally, 3 focus group discussions (FGDs) will be conducted at each study site to identify the barriers that students face to manage their well-being. Two focus groups at each site is considered to be ideal [38]. Consenting participants from the baseline survey will be invited via an email to participate in the FGDs; they will then be given access to the mobile- and web-based platform to generate their initial user profiles. The data gathered from user profiles and FGDs will be used to formulate a student well-being index and also used to design and develop a tailored and context-specific digital health intervention (based on the principle of a human-centered approach) to address the well-being issues of the students. The quantitative data collected from the baseline survey and the qualitative factors will help in identifying causal factors in the environment of the students affecting their well-being [39]. The digital intervention will be based on a human-centered approach and will be designed after understanding an analysis of responses generated from the baseline survey and FGDs. The digital health intervention will be designed as per the needs identified from the FGDs and the baseline survey with population health informatics.

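### The baseline survey is said to help identify causal factors, but one cross-sectional convenience survey analysed by cross tabulation supports only associations among respondents

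*Protocol article*

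**What the plan says.** **Aim.** Study Objective sets aim 1 as "to identify multiple determinants and factors impacting well-being among undergraduate and graduate students".

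**Design.** Study Design and Population states that for aim 1 "a cross-sectional study will be conducted to identify multiple determinants affecting the well-being of the students". It adds: "Five thousand participants will be recruited across Gujarat and Tamil Nadu, India". Students come from five institutes (a university in Gujarat and four colleges in Chennai) and are recruited "using a convenience sampling approach".

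**Causal wording.** This stands in the aim 2 paragraph of the same section. That paragraph takes its quantitative input from the survey: "Baseline data will be collected from aim 1 using predefined questionnaires and validated tools". It then says that these data, with the qualitative factors, "will help in identifying causal factors in the environment of the students affecting their well-being". It also labels aim 2 quasi-experimental.

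**Analysis.** Data Analysis says "A descriptive analysis will be carried out using the baseline data" and that "cross tabulation of sociodemographic factors with variables gathered from the instruments will be done". It also names means, SDs, frequencies, P values, 95% CIs and thematic analysis of the focus groups. College profile, health status, technology familiarity and health behavior are listed there as inputs to the well-being profile. They are not named in the cross tabulation.

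**The concern.** The document claims more than its design can deliver. A survey at one time point cannot show whether short sleep, for example, lowers well-being or follows from it. Convenience recruitment means that who answers may depend on well-being itself. Both limits are fixed by the design, so no analysis plan could remove them.

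The stated association analysis is also a poor match for the aim. Medical, engineering and nursing colleges and a university in another state plausibly differ in gender mix, family income and residence, although the documents give no data on this. A table of well-being by income may then partly be a table of well-being by institute.

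Several candidate factors that the document itself motivates lie outside the stated cross tabulation. Background and Rationale cites a study in Maharashtra in which academic factors and lifestyle predicted stress, and Health Status Profile justifies measuring BMI by its effect on well-being.

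The results feed forward. Aim 2 builds the intervention partly on aim 1, and Ethical Considerations plans to send findings to policy makers.

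**Working it through.** The 5000 comes with no alpha, power, effect size or precision target, so there is no figure of the plan's own to reproduce. The check is mainly a comparison of what is claimed with what the stated elements can support.

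| Needed to support a causal factor | What the document states |
|---|---|
| Exposure known to precede outcome | One cross-sectional survey for aim 1 |
| Known or controlled selection | Convenience sampling |
| Control of confounding, including by institute | Cross tabulation; no adjustment named |
| Candidate factors in the association analysis | Sociodemographic factors only |
| A comparison, if aim 2 is quasi-experimental | None described for that stage |

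The focus groups do not fill these gaps. They can suggest mechanisms, but they do not remove confounding or reverse causation from the survey data.

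**Illustration of crude tables at this sample size.** All inputs except the total of 5000 are assumptions.

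- Factor X has no effect on the outcome and splits the sample 2500/2500.
- A confounder C (for example, type of institute) raises the rate of a poor outcome from 20% to 40%.
- C is present in a fraction a of one X group and b of the other.
- Crude rates are 0.20 + 0.20a and 0.20 + 0.20b.
- The chance of P<0.05 (two-sided) is approximately Φ(difference/SE − 1.96), with SE = √[(p1(1−p1) + p0(1−p0))/2500].

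| C in the two X groups | Crude rates | Odds ratio | Chance of P<0.05 |
|---|---|---|---|
| 55% vs 45% | 31% vs 29% | 1.10 | about 34% |
| 60% vs 40% | 32% vs 28% | 1.21 | about 87% |
| 70% vs 30% | 34% vs 26% | 1.47 | about 100% |

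Middle row in full: p1 = 0.20 + 0.20 × 0.60 = 0.32 and p0 = 0.20 + 0.20 × 0.40 = 0.28. SE = √[(0.2176 + 0.2016)/2500] = 0.01295. Then 0.04/0.01295 = 3.09, and Φ(3.09 − 1.96) = Φ(1.13) = 0.87.

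Within each level of C the true difference is zero by construction, so an analysis that adjusts for C would flag X only at the nominal 5%. The table shows what an unadjusted comparison can do. It is not evidence that a confounder of this strength exists here.

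**The case against.** **The missing model may be in a plan not shown.** This is a condensed article, and a regression model is commonly left to the analysis plan. Data Analysis does not call its list complete and names no method for the randomised comparison either. That stands: the absence of a regression is not the error. What remains is the stated causal claim, which no model fitted to this survey could support, and a stated association analysis narrower than the aim.

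**The wording is hedged.** The causal phrase occurs once, in the aim 2 paragraph, speaks only of helping to identify, and carries a citation. Determinants is ordinary usage in cross-sectional work. A reader might infer that aim 1 itself promises causal findings. It does not; its own text speaks of determinants and factors that impact well-being. The causal phrase nevertheless rests on the aim 1 survey data.

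**The other domains have a stated use.** They go into the well-being profile and the descriptive analysis. That is correct, so they are not unused. They are only absent from the stated association analysis.

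**Stronger readings to avoid.**
- A reader might take the tables to be one factor at a time. The article says only cross tabulation, which could be stratified.
- A reader might conclude that with 5000 students even trivial differences will be significant, citing a half-width of 1.96 × √(0.25/5000) = 1.4 points. That is for a single proportion. For a difference between 2500 and 2500 it is 1.96 × √(2 × 0.25/2500) = 2.8 points, and the first row of the illustration reaches P<0.05 in only about a third of surveys.
- A reader might infer a large design effect from clustering by class. The documents give no class size or intraclass correlation, do not sample by class, and list no class or department variable.

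**Impact on the intervention is limited.** Its content also rests on focus groups and user profiles and is then tested in a randomised trial. That stands; tailoring to reported needs does not require causal estimates.

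**Conclusion.** The concern holds in this form. The aim 2 paragraph claims help in identifying causal factors, while the stated design and analysis can yield only associations among respondents at five institutes. That conclusion follows from the text and needs no assumed numbers. The practical size cannot be taken from the documents. On the assumed inputs, a factor with no effect reaches P<0.05 in about 34% to nearly 100% of surveys, depending on how unevenly the confounder is spread.

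The quasi-experimental label is a secondary wording point, since no comparison is described for aim 2. The randomised evaluation in aims 3 and 4 is not touched by any of this.

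**What to change.** 1. In the aim 2 paragraph of Study Design and Population, replace the causal wording with *factors associated with well-being*. Align Study Objective and Results with it.
2. Remove the quasi-experimental label from aim 2, or state the comparison that justifies it.
3. In Data Analysis, keep cross tabulation as descriptive. Make the main aim 1 analysis a multivariable regression of one named well-being score on the collected baseline domains (sociodemographic, college, health status, technology, health behavior), with institute as a fixed effect. Report adjusted associations with 95% CIs. If the well-being index is itself built from these domains, use an instrument score such as the General Well-Being Schedule, so that predictors are not part of the outcome.
4. Limit inference to respondents at the five institutes.
5. Use clustered standard errors only if class or department is recorded.

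**Cost.** A little more analysis work on data already planned, and a more modest claim; recruitment and the trial do not change. Adjustment does not resolve reverse causation, and mutual adjustment may absorb mediators such as sleep. The plan should therefore state that the coefficients are not to be read causally.

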### Project Timeline and Milestones

A detailed study timeline is presented in Table 1.

**Table 1 table1:** Scheduled timeline of tasks in the student well-being study.

Task	Months									
	1-2	3	4	5	6-7	8-10	11-13	14-15	16-19	20-24
Development of study protocol and ethical approval	✓									
Baseline data collection		✓	✓	✓						
Focus group discussions and development of intervention					✓	✓				
Deployment of the well-being intervention and recruitment of the target sample into intervention and control groups							✓			
Follow-up data collection							✓	✓		
Postdeployment assessment of intervention								✓		
Review of collected data by the research team								✓	✓	
Data analysis									✓	
Scientific publication										✓
Dissemination (report writing and presentations)										✓

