For aim 3 and aim 4, we will perform a randomized controlled trial. Based on the well-being index generated, high-risk individuals will be divided randomly into an intervention group and a control group. The digital health intervention will be a mobile- and web-based platform for students designed to provide tailored well-being–related education and awareness. A human-centered approach will be used to design and develop the intervention by incorporating the students’ needs and preferences to ensure an optimal technology-enabled intervention [40]. The study will also use the HBM in designing the digital health intervention, where HBM will be used as a framework to aid in the factors that influence implementation and the persistence of students in maintaining well-being. The HBM is one of the most widely used theoretical frameworks for understanding behavioral change. The model holds that an individual’s likelihood of adopting and maintaining a new behavior is heavily influenced by their perceptions of the health threat and the behavior being proposed to address that threat [41]. The intervention will include modules for the physical, social, and mental well-being of the students. The study participants will be able to access the personalized, human-centered digital health intervention through their computers or mobile phones depending on the technology platform available to them. The intervention will be tailored and will be delivered via interactive messages addressing the various dimensions of well-being among undergraduates and graduate students. Study participants in the control group will be provided with an educational booklet addressing health information related to student well-being. Pre- and postevaluation of the individuals in the intervention and control groups will be conducted to assess the impact of the digital health intervention. The feasibility, adherence, engagement, and acceptability of the system will be assessed.

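### Table 1 leaves only two months between the end of recruitment and the end of follow-up, so participants entered after the start of month 13 cannot complete the stated 3 months

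*Protocol article*

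**What the plan says.** Two parts of the protocol article bear on how long a randomised participant is observed.

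- **Other Tools, Follow-Up, and Engagement** fixes the duration and its purpose: "Individuals will be followed up for a period of 3 months at regular intervals to assess adherence to the well-being modules". Engagement is tracked in the same paragraph through weekly logins, timely task completion and data submission.
- **Project Timeline and Milestones, Table 1** gives the calendar. The row "Deployment of the well-being intervention and recruitment of the target sample into intervention and control groups" has one tick, in the months 11-13 column. The row "Follow-up data collection" is ticked for months 11-13 and 14-15. The row "Postdeployment assessment of intervention" is ticked for months 14-15 only. Neither of the last two rows has a tick from month 16 on. Data analysis occupies months 16-19, and the plan ends at month 24.

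Under Study Design and Population, the trial for aims 3 and 4 relies on a before-and-after measurement in both arms: "Pre- and postevaluation of the individuals in the intervention and control groups will be conducted".

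**The concern.** The follow-up sentence gives every individual 3 months. The calendar leaves two months between the last permitted recruitment and the close of data collection, so the latest entrants cannot receive what the text states.

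This falls mainly on aim 4, which examines the part played by adherence and engagement. Adherence is the stated purpose of the 3-month period, and counts such as tasks completed can accumulate with time on the platform. If some participants are observed for less time than others, adherence becomes partly a reflection of entry date. Unlike treatment allocation, adherence is not randomised, so nothing in the design removes that mixture. The post measurement sits in the same closing window and would also be taken after shorter exposure in late entrants.

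**Working it through.** **Inputs**

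- Stated follow-up per individual: F = 3 months (Other Tools, Follow-Up, and Engagement).
- Recruitment into the two groups: months 11-13 (Table 1).
- Follow-up data collection: months 11-15 (Table 1).
- Postdeployment assessment: months 14-15 (Table 1).
- Convention adopted here: month m runs from time m − 1 to time m. Recruitment then runs from t = 10 to t = 13, and follow-up closes at C = 15.

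**Step 1. Can the stated 3 months be reproduced for the last entrant?** Available follow-up is A(t) = C − t. At t = 13, A = 15 − 13 = 2 months. The stated figure is not reproduced.

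**Step 2. Who falls short, and by how much?** The shortfall is S(t) = max(0, F − A(t)).

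| Entry | t | Available, 15 − t (months) | Shortfall (months) |
|---|---|---|---|
| Start of month 11 | 10 | 5 | 0 |
| Start of month 12 | 11 | 4 | 0 |
| Start of month 13 | 12 | 3 | 0 |
| Middle of month 13 | 12.5 | 2.5 | 0.5 |
| End of month 13 | 13 | 2 | 1 |

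The last entry time that allows the full period is t = 15 − 3 = 12, the boundary between months 12 and 13. Entry exactly at the start of month 13 just suffices; any later entry does not.

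**Step 3. What share is affected?** It equals the share recruited after t = 12. The article gives no accrual rate. Under even accrual (an assumption) the share is (13 − 12)/(13 − 10) = 1/3. It is zero if all recruitment is finished by the start of month 13, and above one third if accrual is weighted towards the end.

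**Step 4. What would reconcile the two?**

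- Move the close to the end of month 16: A(13) = 16 − 13 = 3 months.
- Or keep C = 15 and end recruitment at t = 12, the end of month 12: A(12) = 15 − 12 = 3 months.

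**The case against.** The strongest reply is that the calendar can be read consistently. The months 11-13 column is exactly three months long and names deployment and recruitment in one row. The trial draws on students already surveyed at baseline in months 3-5, so the high-risk group could be randomised in one batch at the start of month 11, use the platform for three months, and be assessed in months 14-15. On that reading nobody falls short.

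This is possible, but the article does not say it. The row places recruitment across the whole of months 11-13 without restriction. Follow-up data collection still ticked in months 14-15 also fits poorly with a cohort whose three months would have ended with month 13. If batch randomisation is intended, one sentence saying so removes the conflict.

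It can also be said that a chart with multi-month columns is not a visit schedule, and that a condensed article leaves visit windows to the full protocol. That is fair for the absence of a visit window, which is not held against the article here. It does not answer a disagreement between a duration and a calendar that are both stated.

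Other parts of the reply stand. The shortfall is at most one month. The 3 months is tied to adherence, and the outcome tools are described only as used before and after the intervention, with no month attached. Both arms share the same recruitment and assessment windows.

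**Conclusion.** The inconsistency is real and moderate in size. As written, participants entered after the start of month 13 have 2 to 3 months of possible follow-up against the 3 stated. They make up about one third of the sample if accrual is even, an assumption the article neither supports nor excludes. The consequence is truncated or unequal exposure in the adherence and engagement data, and in the post measurement for late entrants.

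Three stronger conclusions might be inferred and are not supported:

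- **That the comparison between arms is biased.** Randomisation should balance entry date between groups. The contrast would average over somewhat unequal durations, which is not bias.
- **That a 3-month treatment effect is promised and then missed.** The article names no such endpoint; the 3 months is attached to adherence.
- **That times to assessment are widely scattered, with most participants assessed too early.** This needs assessment dates spread over months 14-15 without regard to entry date, and nothing in the article describes such a pattern.

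**What to change.** Reconcile the follow-up paragraph with Table 1 before randomisation starts, since follow-up time that is not collected cannot be recovered. Either of two changes is enough:

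1. Extend the follow-up data collection and postdeployment assessment rows of Table 1 to month 16. The cost is at most one month of overlap with data analysis, which already spans months 16-19 of a 24-month plan.
2. State that randomisation closes by the end of month 12, leaving the follow-up rows as they are. The cost is a recruitment period one month shorter.

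With either choice, add a sentence to the follow-up paragraph that times the post assessment at 3 months from each participant's own randomisation, in both arms. The whole change is one sentence and a few table cells.
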